### Procedure

2.5

Screening, recruitment, and treatment of our patients take place in our emergency department. Initially, the patient's medical history along with the accident history is obtained. All patients with fingertip amputations who present themselves to the emergency department are informed about this clinical trial. The injury is examined and the inclusion respectively exclusion criteria are checked. We routinely perform an X-ray examination to exclude bony injuries. Additionally women of childbearing age have to provide a pregnancy test prior to that. In case all inclusion and no exclusion criteria are fulfilled patients get comprehensively informed about the clinical trial and the informed consent is obtained by the trained surgeon. Randomization takes place through prepared nontransparent and consecutively numbered envelops and determines the initial treatment group (conventional film dressing or silicone finger cap). Afterwards, the respective occlusive dressing is applied according to the randomization result. We check the dressing 1 day after initial application for correct fitting. Afterwards we conduct clinical controls weekly to check for correct fitting of the occlusive dressing, to enquire possible adverse events and serious adverse events, and to take photos of the dressing and possibly of the wound. In case, the patient has got a silicone finger cap we aspirate wound fluid out of the reservoir to examine the microbiological colonization of the wound. If the patient has got an occlusive film dressing, no microbiological examination can be performed except for an initial smear and a 2nd smear when the film dressing is removed after 2 weeks. As a substudy of this clinical trial, excess wound fluid that is not used for microbiological analyses is preserved at −80 °C for future proteome analyses. Furthermore, patients are asked to complete a modified quality of life Wuerzburg Wound Score at each of their visits.

On day 14 after the injury, the occlusive dressing method is changed. Patients treated with the conventional film dressing get a silicone finger cap and vice versa. Further 14 days later the patient decides which dressing she or he respectively the guardians would prefer for the remaining treatment if needed before the dressing is removed. The chosen treatment is then applied if further treatment is needed. At day 42 after the injury the treatment of the wound is orderly finished and the wound should be reepithelialized. The occlusive dressing is removed and photographs of the injury site are taken. If the wound is not fully epithelialized at this point, a conventional film dressing is used as long as further occlusion is needed. Final follow-up examination takes place 4 months after the injury. At the follow-up we test the function of the perspiratory glands and the regeneration of the fingerprint using Moberg Ninhydrin test.^[19]^ Also the range of motion in the distal interphalangeal, proximal interphalangeal and metacarpophalangeal joints, and the 2-point-discrimination threshold in the area of the injury is checked in comparison to the corresponding finger of the contralateral hand.^[20]^ Moreover, we also measure the soft tissue thickness above the bone in the region of the healed injury using medical ultrasound. Finally, patients have to complete a follow-up questionnaire. At each visit the dressing or, when applicable, the exposed finger is photographed from all perspectives. High definition photographs will be digitally analyzed and kept for documentation purposes. In this study, we will introduce a new volume-rendering method for monitoring finger growth 3-dimensionally. Photographs will be rendered in 3-dimensional models and advanced 3-dimensional segmentation, and filtering algorithms will be used to measure volume progress of the injured finger. This method will allow monitoring of tissue recovery in micrometers quality.

### Statistics

2.6

#### Proposed sample size

2.6.1

There is no certified medical device available for the conservative management of fingertip amputation injuries. Opsite Flexigrid (Smith & Nephew Medical Limited, Hull, England) has not been certified for full thickness amputations injuries as described, and our novel finger cap has never been used before in a controlled trial. Therefore, this study is per definition a pilot study that has to be limited to a small sample size in order to comply to German and European legislation as well as to guidelines of good clinical practice.

The primary objective is the rate of patients who decide for the silicone finger cap at day 28. At this point they have experienced both methods (conventional film dressings and silicone finger cap) for 2 weeks each. This rate can be regarded as a measure of the acceptance of the silicone finger cap. If 80% of the patients in this study decide for the silicone finger cap we consider the hypothesized superiority of the finger cap as verified. Assuming that approximately 80% of the patients decide for the silicone finger cap, 20 patients (95% confidence interval, one-sided, 65% lower limit, the distance from the rate to the lower limit of the confidence interval is at most 15%) are needed (Program nQuery-Advisor 6.01, Copyright^©^ 1995–2005, Janet D Elashoff). When considering 2 possible drop-outs, 22 patients must be included.

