**Methods and analysis::**

By employing an innovative pseudo-cross-over-design with a dichotomous primary endpoint based on patients preference, this pilot study will gain statistically significant data with a very limited sample size. Our RCT will investigate acceptance, safety, effectiveness, and efficacy of this novel medical device while gathering information on the clinical course and outcome of conservatively treated fingertip injuries. A total of 22 patients older than 2 years will be randomly assigned to start the conservative treatment with either the traditional film-dressing or the novel finger cap. The treatment will be changed to the other alternative for another 2 weeks before the patient or the guardian is confronted with the decision of which method they would prefer for the rest of the treatment (if required).

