### Statistical analysis

2.8

A list of imaginable complications and risks with possible management plans is part of the study protocol. In case of changes in the treatment due to complications or patient requests, patients can be treated accordingly in our clinic. All randomized patients who will be treated with the silicone finger cap or the film dressing will be included in the intent-to-treat-analyses.

The primary objective of the study is to verify the hypothesis that the silicone finger cap is superior to the conventional film dressing in regards to its acceptance by the patients/guardians. The primary endpoint is the rate of patients who decide up to day 28 to continue their treatment with the silicone finger cap. If this rate is at least 80% and the lower limit of the confidence interval is not less than 65%, the silicone finger cap is considered to be much better accepted than the conventional method.

The secondary target parameters are exploratively evaluated. Secondary endpoints are analyzed according to their scale level: for steady endpoints, mean and standard deviation, or medians and quartiles (graphically corresponding to confidence intervals or boxplots), for the categorical endpoints absolute and appropriate relative frequencies are used. Depending on the distribution of the variables to be analyzed the *t* test, the *U* test and the Chi test^[2]^ are used. For paired comparisons, the paired *t* test is used in the case of normally and the Wilcoxon test in the case of nonnormally distributed variables. Sub-group analyses according to patient age, injury severity, and mechanism of injury will be performed if possible. The statistical analysis is carried out using the SPSS program system (International Business Machines Corp. [name]) and the SAS System (SAS Institute Inc., [name]) for Windows program in the currently available versions.

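### The success bar of 80% observed preference equals the assumed true rate and sits well above superiority, so the trial misses it 37% to 46% of the time even if its assumption is right

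*Protocol article*

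**What the plan says.** Section 2.8 (Statistical analysis) gives the primary objective as to "verify the hypothesis that the silicone finger cap is superior to the conventional film dressing in regards to its acceptance". The endpoint is the share of patients or guardians who choose the cap at day 28, after two weeks on each dressing.

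Section 2.6.1 (Proposed sample size) sizes the trial on precision: "Assuming that approximately 80% of the patients decide for the silicone finger cap, 20 patients" are needed, with the specification "95% confidence interval, one-sided, 65% lower limit" and the condition that "the distance from the rate to the lower limit of the confidence interval is at most 15" points. It then allows for losses: "When considering 2 possible drop-outs, 22 patients must be included". The same section gives a success criterion: "If 80% of the patients in this study decide for the silicone finger cap we consider the hypothesized superiority of the finger cap as verified".

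Section 2.8 gives a two-part criterion: "If this rate is at least 80% and the lower limit of the confidence interval is not less than 65" per cent. Its conclusion is that the cap is much better accepted than the film, and the section does not say which result would confirm superiority itself.

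The Abstract says that "this pilot study will gain statistically significant data with a very limited sample size", and the Introduction repeats the promise.

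**The concern.** Three things do not fit together.

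- **Threshold and assumption coincide.** If the true rate is what the plan expects, the observed rate falls on either side of it with roughly equal chance. The trial can then fail for no reason other than sampling variation.
- **The bar does not match the hypothesis.** In a choice between two dressings, superiority in acceptance most naturally means that more than half choose the cap. The bar is 80%. A clear preference could therefore be reported as superiority not verified.
- **Two sections state different rules for the primary endpoint.** One has a single condition and concludes superiority. The other has two conditions and concludes something stronger. Whether they can disagree on the same data depends on an interval method that is not named.

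At stake is the trial's only confirmatory conclusion, and the promise of statistically significant data made for it.

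**Working it through.** **Inputs.** From 2.6.1: assumed rate 0.80, one-sided 95% limit, 65% lower limit, 15-point distance, 20 evaluable and 22 included patients. From 2.8: observed rate at least 80% and lower limit at least 65%; all randomised and treated patients are analysed, so n may be 20, 21 or 22. The 50% null used in step 5 is an assumption, inferred from the two-way choice.

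**1. The plan's own figure.** With a one-sided normal-approximation (Wald) limit, n = z² p(1 − p)/d² = 1.645² × 0.8 × 0.2 / 0.15² = 19.24, rounded up to 20. Adding 2 drop-outs gives 22. The stated sample size is reproduced. A two-sided 95% interval would give 27.3, hence 28, so the one-sided Wald limit is the reading that fits.

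**2. Chance of reaching 80% observed when the true rate is 80%.** Let r be the smallest count with r/n ≥ 0.80, and X binomial(n, 0.80).

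| n | r | P(X ≥ r) | Failure |
|---|---|---|---|
| 20 | 16 | 63.0% | 37.0% |
| 21 | 17 | 58.6% | 41.4% |
| 22 | 18 | 54.3% | 45.7% |

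More patients would not cure this. The same probability is 56% at n = 100 and 52% at n = 1000.

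**3. Effect of the 65% limit in section 2.8.** The table gives the one-sided 95% lower limits at the smallest count that reaches 80%.

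| Result | Wald | Exact (Clopper-Pearson) |
|---|---|---|
| 16/20 | 0.653 | 0.599 |
| 17/21 | 0.669 | 0.616 |
| 18/22 | 0.683 | 0.631 |

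Under Wald, all three pass. The second condition adds nothing, the two sections give the same verdict, and the failure rates of step 2 stand.

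Under the exact limit, all three fall below 65%. Section 2.6.1 would then call superiority verified while the section 2.8 rule is not met. The counts needed become 17/20 (limit 0.656), 18/21 (0.671) and 19/22 (0.684). Success at a true 80% falls to 41.1%, 37.0% or 33.2%, so failure is 58.9%, 63.0% or 66.8%.

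**4. False positives.** If the true rate is 50%, the probability of reaching 80% observed is 0.6% (n = 20), 0.4% (n = 21) or 0.2% (n = 22).

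**5. A rule matched to superiority.** Exact one-sided 5% binomial test of preference above 50%:

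| n | Success at | Actual error at 50% | Power at 80% |
|---|---|---|---|
| 20 | ≥ 15 | 2.1% | 80.4% |
| 21 | ≥ 15 | 3.9% | 89.1% |
| 22 | ≥ 16 | 2.6% | 86.7% |

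A result of 15/20 (75%) has exact one-sided p = 0.021 against 50% and an exact lower limit of 54%. Under the plan as written it does not count as superiority.

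**The case against.** The strongest reply is that a demanding bar is legitimate. This is a pilot of a new device, deliberately small, sized on precision and making no claim about power. The sponsor makes the caps, and a bar of 80% guards against over-claiming. The assumed rate is also only approximate: at a true 85%, failure under the 80% rule falls to 17.0% (n = 20) or 22.6% (n = 22). All of this stands. It supports keeping the high bar for a strong claim, but not leaving its chance of success unstated or using it as the only route to a claim of superiority.

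Three stronger readings are tempting, and the protocol does not support them.

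- **That the rule is no test of superiority.** This fits the bare sentence in 2.6.1, but not section 2.8. A lower limit of 65% excludes 50%, so every success under that rule is also evidence of superiority. Even the smallest counts that reach 80% are significant against 50%: exact one-sided p is 0.006 at 16/20, 0.004 at 17/21 and 0.002 at 18/22.
- **That the two sections necessarily give opposite verdicts.** They do so at 16/20, 17/21 and 18/22 only if the limit is exact. Under the Wald limit that reproduces the sample size they agree, and an analysis plan that is not shown may name the method. What remains in any case is that the stated conditions and the conclusions drawn from them differ.
- **That the sample size is wrong.** It is reproduced as a precision calculation. The difficulty lies in the decision rule.

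**Conclusion.** The point holds as a mismatch between bar, assumption and hypothesis. At a true rate of exactly 80%, the trial misses its own bar 37.0% to 45.7% of the time for 20 to 22 patients. That range applies to the rule in 2.6.1, and to the rule in 2.8 if its limit is Wald; with an exact limit the range is 58.9% to 66.8%. The promise of statistically significant data is therefore not a property of the design.

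The error risked is a false negative, not a false positive, and for that reason this is a should-fix and not a must-fix. The failure rates rest on independent choices with a common true rate of 80%. The comparison with a superiority test rests in addition on a 50% null, which the protocol does not state.

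**What to change.** 1. Use one decision rule, in the same words, in 2.6.1 and 2.8, and name the method for the one-sided 95% interval.
2. Judge the superiority hypothesis by an exact one-sided 5% binomial test of preference above 50%: success at 15 or more of 20, 15 or more of 21, or 16 or more of 22. State the 50% null explicitly. Keep the 80% rate with the 65% lower limit as a second, higher label (much better accepted).
3. In the Abstract and the Introduction, replace the promise of statistically significant data with the computed probabilities of success for both levels.

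The cost is wording only, with no extra patients. There are two downsides. Superiority would be declared at an observed rate of 71% to 75% (15/21 = 71.4%, 16/22 = 72.7%, 15/20 = 75.0%) and no longer only at 80%. The modest chance of reaching the higher label would also become visible. If the sponsor prefers the high bar as the only criterion, its probability of success and a single conclusion should still be stated.

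### The 65% lower limit and 15-point precision at n = 20 hold only under the one-sided Wald approximation, and the success rule that uses this limit names no interval method

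*Protocol article*

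**What the plan says.** Section 2.6.1 (Proposed sample size) of the protocol article gives the size as follows: "Assuming that approximately 80% of the patients decide for the silicone finger cap, 20 patients" are needed, on the basis of a 95% confidence interval, "one-sided, 65% lower limit, the distance from the rate to the lower limit of the confidence interval is at most 15" per cent. The software is named ("Program nQuery-Advisor 6.01"), but the interval formula is not. Two patients are added: "When considering 2 possible drop-outs, 22 patients must be included". The same section gives a success statement with no confidence limit in it: "If 80% of the patients in this study decide for the silicone finger cap we consider the hypothesized superiority of the finger cap as verified".

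Section 2.8 (Statistical analysis) gives the primary verdict rule with two conditions: "If this rate is at least 80% and the lower limit of the confidence interval is not less than 65" per cent, the cap counts as much better accepted. This sentence does not repeat the confidence level or the sidedness, and it names no interval method.

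**The concern.** The 65% limit does two jobs. In 2.6.1 it is the precision claim that justifies 20 patients. In 2.8 it is half of the primary decision rule. With 20 patients and a rate near 80%, common methods for a binomial limit differ by several percentage points, and the planned margin over 65% is only a fraction of a point. The choice of method can then decide the verdict at the result the sponsor assumes. If the method is settled after the count is known, the analyst in effect chooses the verdict. If it is the method that produced n = 20, the limit does not have the 95% confidence attached to it.

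**Working it through.** **Inputs.** Rate p = 0.80, one-sided 95% (z = 1.645), distance d = 0.15, lower limit 0.65, 20 evaluable and 22 enrolled (all from 2.6.1). Success rule: rate at least 0.80 and lower limit at least 0.65 (2.8).

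**1. The plan's own figure.** Wald precision formula: n = z² p(1 − p)/d² = 1.645² × 0.16 / 0.0225 = 19.24, rounded up to 20; 20 + 2 = 22. This reproduces. The two-sided version gives 27.3 (28) and does not, so 20 rests on the one-sided Wald formula.

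**2. One-sided 95% lower limits at 16/20.**
- Wald: 0.80 − 1.645 × √(0.16/20) = 0.80 − 0.147 = 65.3% (distance 14.7 points).
- Wilson: [0.80 + z²/40 − z√(0.16/20 + z²/1600)] / (1 + z²/20) = (0.8676 − 0.1619)/1.1353 = 62.2% (17.8 points).
- Exact (Clopper-Pearson): the p that solves P(X ≥ 16 | 20, p) = 0.05, which is 59.9% (20.1 points).

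Six further one-sided methods were tried: Wald and Wilson with continuity correction, Jeffreys, mid-P, Agresti-Coull and logit. They give 59.4% to 62.8%. Of the nine, only plain Wald reaches 65%.

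**3. Smallest counts with an observed rate of at least 80%, and the next count up.**

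| Count | Rate | Wald | Wilson | Exact |
|---|---|---|---|---|
| 16/20 | 80.0% | 65.3% | 62.2% | 59.9% |
| 17/20 | 85.0% | 71.9% | 67.8% | 65.6% |
| 17/21 | 81.0% | 66.9% | 63.7% | 61.6% |
| 18/21 | 85.7% | 73.2% | 69.1% | 67.1% |
| 18/22 | 81.8% | 68.3% | 65.1% | 63.1% |
| 19/22 | 86.4% | 74.3% | 70.4% | 68.4% |

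The 2.8 rule is therefore met from 16/20, 17/21 or 18/22 under Wald; from 17/20, 18/21 or 18/22 under Wilson; and from 17/20, 18/21 or 19/22 under exact.

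**4. Operating characteristics (binomial tails).**

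| Rule | Met if true rate is 65% | Met if true rate is 80% |
|---|---|---|
| ≥ 16/20 (Wald) | 11.8% | 63.0% |
| ≥ 17/20 (exact; also Wilson) | 4.4% | 41.1% |
| ≥ 18/22 (Wald; also Wilson) | 7.2% | 54.3% |
| ≥ 19/22 (exact) | 2.5% | 33.2% |

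At n = 21 and a true rate of 65%, the Wald rule (≥ 17) is met with probability 9.2% and the exact rule (≥ 18) with 3.3%. The actual coverage of the Wald limit at a true rate of 65% and n = 20 is 100 − 11.8 = 88.2%.

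**5. Redundancy under Wald.** At a rate of 80% and n = 20 the Wald distance is 14.7 points. It shrinks as n grows or as the rate rises above 80%. Any observed rate of at least 80% with 20 or more patients therefore clears 65%, and the second condition in 2.8 does no work.

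**6. Size at which an observed 80% clears 65% exactly.** Checked in steps of five, the exact limit is 64.3% at 24/30 and 65.7% at 28/35.

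**The case against.** A reader might infer that the sample size is an arithmetic error, or that the planned result fails the plan's own criterion. The documents support neither. The figure of 20 reproduces, and under the formula behind it 16/20 gives 65.3% and meets both conditions in 2.8. Failure arises only under an interval that the article does not prescribe.

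A reader might also infer that a stated 5% type I error is breached. The article states no type I error rate and no null hypothesis of 65%; it states a 95% confidence level. The 11.8% is a shortfall in coverage against that level. Nor does the choice of interval put in doubt that the cap is preferred at all: even the exact limit at 16/20 (59.9%) excludes 50%, and P(X ≥ 16 | 20, 0.5) = 0.006. What turns on it is the plan's own 65% margin.

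Other points for the plan also stand. Taking the interval in 2.8 to be the one-sided 95% interval of 2.6.1 is the natural reading, so not repeating those words is no contradiction. The formula may be named in an analysis plan that is not shown. The split between methods narrows if all 22 patients are analysed: 18/22 passes by one-sided Wilson (65.1%) and even by two-sided 95% Wald (65.7%), and fails by exact (63.1%). Exact is also not the only defensible choice.

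These points do not remove the core. The article itself prints the 65% limit and the 15-point distance as what 20 patients deliver, and builds the verdict on that limit. Both figures depend on an approximation that falls clearly short of 95% at this size.

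**Conclusion.** The point holds in a limited form. The stated precision is obtained only with the one-sided Wald approximation. With Wilson or exact limits the distance at 16/20 is 17.8 or 20.1 points, and the limit is about 62% or 60%. At 16/20 and 17/21 the verdict in 2.8 is a pass under one-sided Wald and a fail under Wilson or exact; at 18/22 only the exact limit of these three fails. If Wald is the intended method, its coverage at a true rate of 65% is about 88% at n = 20, and the 65% condition adds nothing to the 80% condition.

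This rests on reading the interval in 2.8 as one-sided 95%, on 20 to 22 patients with a recorded preference, and on independent binomial responses. It corrects a precision figure and an unnamed method in the decision rule. It does not show a miscalculated sample size. Which small-sample interval to adopt is open to debate.

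**What to change.** - **Section 2.6.1:** keep 22 patients, but restate the precision for a valid small-sample interval. At 16/20 the one-sided 95% lower limit is about 60% (exact) or 62% (Wilson), a distance of about 18 to 20 points.
- **Section 2.8:** before data review, name the one-sided 95% interval used for the 65% criterion and list the success counts it implies. For the exact limit these are at least 17/20, 18/21 or 19/22.
- **Reconcile the two sections.** Section 2.6.1 says an observed 80% verifies superiority. Under an exact rule 16/20 would not succeed, and the effective threshold becomes 85% to 86%. One of the two statements has to give way.
- **If the Wald rule is kept:** say so, state its coverage of about 88% at a true rate of 65% and n = 20, and state that the 65% condition is then redundant.

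**Cost.** No extra patients, but more than a change of wording if the exact rule is adopted. At the assumed true rate of 80%, the chance of success falls from 63.0% to 41.1% with 20 patients, or from 54.3% to 33.2% with 22, and the article should disclose this. Wilson gives the same loss as exact at n = 20 and none at n = 22, where its count of 18 is met with probability 7.2% at a true rate of 65%. Letting an observed 80% clear an exact 65% limit would take roughly 35 evaluable patients, which conflicts with the small size that 2.6.1 says a pilot must keep to.
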